### Data and safety monitoring committee

All data collected from participants will be recorded and secured on to physical- and cloud-based environment, certified for medical data. A separate secure file will contain contact information but has no personal data or protected health information that is collected as part of the study. Data will be collected at these intervals: only the research assistants/associates who have completed human research training will have access to the individually identifiable information about the participant and his/her family. Data will be collected by trained research assistants who have completed on-line training in human subjects’ research, HIPAA, and research integrity, training at each site on research data management and confidentiality. No personally identifying information will be coded on questionnaires, interviews, or other scoring forms, to protect confidentiality. Unique subject identification numbers are assigned to each participant. Only the Principal Investigator and key personnel who are HIPAA-trained have access to the file that links names with subject numbers, which will be stored separately from the de-identified data. All data will be stored in locked file cabinets in a locked office (paper/pencil files) and on password-protected computers located behind a secure and maintained firewall. Moreover, data will be collected specifically for this proposed research project.

All data will be anonymized for publication. Only researchers affiliated with the study will have access to participant data.

### Statistical analysis

Databasing, statistical software, and implementation of analyses will be programmed in the SAS Version 9.4, implemented along with plotting and graphing options. EEG analyses (e.g., mixed effects models) will be implemented at the Region of Interest (ROI) as well as the whole brain level.

#### Descriptive statistics

The following descriptive statistics will be presented:

▪ For quantitative variables: number of non-missing values, number of missing values, mean, standard deviation, minimum, maximum; median and first and third quartiles.▪ For categorical variables: number of non-missing values, number of missing values and percentage. Unless otherwise specified, percentages will be calculated using the number of non-missing values as the denominator (i.e., not including missing values). Where appropriate, confidence intervals for proportions will be calculated using the adjusted Wilson score method (64).

#### Reference interval

There are several methods for constructing a reference interval for psychometric measures based on age and gender, all of which require a larger number of subjects the higher the precision desired. The minimum number of observations required per group has been set at 120 and reaffirmed in the National Committee for Clinical Laboratory Standards guidelines (65). For a 95% confidence interval around each percentile at the ends of the reference interval, this number increases to 153, and to 199 for a 99% confidence interval.

We will thus examine performance on neuropsychological tests, questionnaires, and academic assessments by:

▪ A univariate ANOVA to test for main effects and moderating effect of a qualitative variable.▪ Linear multiple regressions and conditional analysis to test the moderating effect of a quantitative variable.▪ And multiple linear regressions to test a mediating effect.

Machine- and deep-learning approaches will be used also to map the multi-dimensional of the cognitive, emotional, and behavioral measures. Unsupervised machine learning approaches will be to identify groups of children across dimensions and define transdiagnostic profile according to common cognitive, emotional, or behavioral profiles. Such methods will include class-based analyses (e.g., latent class or cluster analyses) and clustering algorithms.

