### Primary objective

The primary objective of the study is to determine whether a normative base relying on multimodality biometry e-measurements tool, called XAI4Kids®, can evaluate brain functioning, i.e., the psychometric properties (sensitivity, specificity, reliability, reproducibility, and positive/negative predictive values) in children aged 7 to 12 years and evaluate the efficiency and acceptability of such e-screening tool compared to various current convergent validity measures of brain functioning (Figure 2).

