### Participant

The inclusion criteria will be: (i) boys or girls of any ethnicity, aged 7–12 years (typically developing and diagnosed with NDDs); (ii) French native speakers; (iii) normal hearings, normal or corrected-normal vision; (iv) no brain trauma; (v) an estimated intelligence quotient of 85 and above (exclusion if score < 25th percentile) based on Weschler’s subtests Matrix Reasoning and Similarities (50); (vi) no history of co-morbid psychiatric illness that might confound the analysis of the study (e.g., schizophrenia, obsessive-compulsive disorder, major depression, or bipolar disorder); (vii) ADHD medications and Selective serotonin reuptake inhibitors (SSRIs) are not exclusionary since use of these medications is associated with neurodevelopmental disorder condition, but the treatment will be suspended 2 days before any cognitive evaluation.

The exclusion criteria will be: (i) failure to meet the inclusion criteria; (ii) lack of written informed consent: the child and at least one of the parents (or the legal representative) must sign the informed consent form.

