#### Sampling

We will account for variations across population and strive to identify the broad range of social and environmental influences on brain function and development. Such an approach may ultimately reveal a much more complex tapestry of etiological mechanisms than are typically derived from averaging over a relatively homogenous sample. Based on our own experience and previous sampling frame to access a representative sample of the larger heterogeneous population of children (66–69) and using three broad dimensions of phonological processing abilities, executive skills and processing speed (70) with latent factor analysis (71), we estimated that the final sample size is 400 children (half boys and half girls) for power analysis of 0.8, a confidence level of 0.05, and a type I error to detect medium to small effects over the study’s duration (72) Because we except a 20% attrition rate at each critical step: the enrollment process till the data collection completion, we have estimated that 786 participants (Figure 1) will be needed to provide a comprehensive understanding of changes through the test batteries assessing numerous factors impacting brain functioning.

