## Discussion

We have described EPIDIA4Kids, a study protocol to evaluate how multimodality biometry relying on digital epidemiology can give insight into brain functioning in children aged 7 to 12 years. While they are playing psychometric games on an unmodified tablet, multi-stream data will be collected from 400 children volunteers independently of NDD diagnosis.

Multivariate linear models for brain functioning scores will be obtained by using supervised machine/deep-learning and cross-validation. Those models will include variables from the collected biometric data such as emotion estimates, eye-tracking features, digit-trajectories, correction rates and response time during game’s performances. Each brain functioning scores estimated by each biometric model will be agreed with each score of one or some questionnaires. This multimodality approach (73) reflects the recent advances in both quantity and quality of data available since Information & Communication Technology (ICT) and Internet of Things (IoT) brings high potential for improved accuracy at cost-efficiency (24, 28). Machine learning and AI applied to NDDs may open valuable route to examine heterogenous symptoms in pediatric population and at individual level, by integrating multimodality dimensions in prediction models, such as social, environmental, and structural determinants (74–76). Furthermore, the models can handle for missing data and larger numbers of interactive predictors. The so-called digital epidemiology could thus provide support more accurate and objective diagnostic and therapeutic decision making to health practitioners in their practice.

However, while we aim at building comprehensive datasets to create meaningful metrics of cognition, emotions and behaviors based digital epidemiology, we will carefully review data quality to lower response bias (e.g., youth’s illectronism, intra-and inter-examiner variance) by, for instance, minimizing heterogeneity of hardware implementation, and AI-related bias (e.g., over/underfitting). Furthermore, these *de novo* biometrics will require mix adjustment to ensure that observed differences in outcomes are relevant to the actual clinical categorization.

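### With 400 children, no joint age-by-sex partition reaches the plan's own 120 per reference group, no listed analysis estimates a reference limit, and the reference population is not defined

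*Protocol article*

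**What the plan says.** Under Aims of the study, the protocol article makes a normative database of brain functioning at ages 7 to 12 the primary aim. The Reference interval section speaks of "constructing a reference interval for psychometric measures based on age and gender". It says several methods exist and commits to none. It then states that "The minimum number of observations required per group has been set at 120". For a 95% confidence interval around each limit, "this number increases to 153, and to 199 for a 99% confidence interval". No groups, age bands or estimation method are named. The section continues directly with ANOVA, moderation and mediation regressions, and clustering.

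The Sampling section says that "the final sample size is 400 children (half boys and half girls". It justifies this by a power statement for medium to small effects, with no reference to the 120.

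On who makes up the sample, the Participant section admits children "aged 7–12 years (typically developing and diagnosed with NDDs". The Recruitment section draws on the community, outpatient clinics and physician referrals, and adjusts recruitment to sociodemographic targets only. The Discussion says that "multi-stream data will be collected from 400 children volunteers independently of NDD diagnosis". The Participant section also requires an estimated IQ of 85 or more and excludes brain trauma and several psychiatric illnesses. The Primary objective lists "sensitivity, specificity, reliability, reproducibility, and positive/negative predictive values" among the properties to be evaluated.

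**The concern.** The 120-per-group rule is the only precision standard the article gives for its primary deliverable, and the sample was not sized to it. If intervals are built for age and sex jointly, every cell falls short. If they are not, the article does not say what replaces them, because none of the tests it lists yields a percentile limit.

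The second question is whom the norm describes. A reference sample can be children without a diagnosis, or the whole population with NDD children at their natural frequency. This one is neither by design: the NDD share is whatever recruitment produces. The limits decide which children are called atypical, so an undefined reference population carries straight through to the tool's use.

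**Working it through.** **Inputs from the article.** 400 completers, 200 per sex; ages 7 to 12, i.e. six single years; minima of 120, 153 and 199 per group; 20% attrition at each step. Assumption: children are spread evenly over age.

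**The plan's own figures.** The non-parametric rule for a confidence interval at the 2.5th percentile needs 0.975^n ≤ (1 − confidence)/2. At 90% confidence, n = ln(0.05)/ln(0.975), rounded up to 119, against the stated 120. The same rule gives 146 at 95% (stated 153) and 210 at 99% (stated 199). Those two do not match, so their source probably uses a different rule; nothing below depends on it. For attrition, 400/0.8³ = 781, against 786 planned.

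**Group sizes from 400, and precision.** For a normal score, the SE of the 2.5th percentile in SD units is sqrt((1 + 1.96²/2)/n) = sqrt(2.92/n).

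| Partition | Groups | n per group | Reaches 120? | SE (SD) | 95% half-width (SD) |
|---|---|---|---|---|---|
| Sex only | 2 | 200 | yes (also 153, 199) | 0.12 | 0.24 |
| Three age bands only | 3 | 133 | yes (not 153) | 0.15 | 0.29 |
| Two age bands × sex | 4 | 100 | no | 0.17 | 0.34 |
| Three age bands × sex | 6 | 67 | no | 0.21 | 0.41 |
| Single years only | 6 | 67 | no | 0.21 | 0.41 |
| Single years × sex | 12 | 33 | no | 0.30 | 0.58 |

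A group of exactly 120 has SE 0.16 and half-width 0.31. At n = 33 the non-parametric rank of the 2.5th percentile is 0.025 × 34 = 0.85, below the lowest observation; 0.025 × (n + 1) = 1 needs n = 39.

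Completers needed for 120 per cell are 4 × 120 = 480, 6 × 120 = 720 or 12 × 120 = 1,440. Divided by 0.8³, that means recruiting about 938, 1,407 or 2,813. The Figure 1 legend conflicts with itself by expecting about 500 at follow-up after 400 at baseline. Even 500 would give 125 only for two bands × sex, then 83 and 42.

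**Precision of the alternative.** The simulated SE of the 2.5th percentile with a quadratic age term, sex and a constant SD on 400 children at six discrete ages is 0.11 to 0.14 SD. With the SD modelled in age and sex it is 0.14 to 0.19. With continuous age as well, it is about 0.22 at the youngest and oldest ages.

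**Two opposing shifts in the lower limit.** The sizes are assumptions, because the article gives neither the NDD share nor the score deficit.
- Pooling NDD children: solve (1 − s)Φ(x) + sΦ(x + d) = 0.025. For s from 0.1 to 0.5 and d of 0.5 or 1 SD, the limit moves outward from −1.96 to between −2.04 and −2.68 SD. At s = 0.1 and d = 1 it is −2.18, a shift of 0.22 SD.
- Excluding IQ below 85: solve P(Y < x | IQ z-score > −1) = 0.025. With an assumed score–IQ correlation of 0.5 or 0.7, the limit moves inward to −1.70 or −1.51 SD, a shift of 0.26 or 0.45 SD.

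Either can dominate within plausible ranges.

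**The case against.** The article says several methods exist and names none. It reports 120 as a guideline minimum per group and never defines a group as an age-by-sex cell. A reader might infer that no age- or sex-based interval can meet the standard, or that 1,440 children are required. The documents support neither: sex alone and three age bands alone pass, and 1,440 presumes single-year-by-sex cells that appear nowhere. This part of the objection stands. What remains is that the section speaks of age and gender together and gives a per-group number that no joint split of 400 can satisfy.

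A reader might also infer that including NDD children is an error that moves the cut-off outward and hides affected children. That does not follow. The aim is dimensional and transdiagnostic, and a population norm properly contains NDD children at their prevalence. Only uncontrolled enrichment is a problem, its extent is unknown, and the IQ and psychiatric exclusions pull the other way.

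Nor does the article say that predictive values will be computed at the sample's case share; it only lists them as properties to evaluate.

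Finally, the norming method and any weighting may stand in a full protocol or SAP that is not shown, and their absence from a condensed article is no finding by itself. But the sample size, the per-group minimum, eligibility and recruitment targets are stated here. A later plan can choose a method, but it cannot enlarge the cells or set an NDD quota once recruitment has closed.

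**Conclusion.** The point holds in bounded form. The stated minimum and the stated sample are incompatible for every joint age-by-sex partition. The shortfall is 20 per cell in the coarsest split (100 against 120) and 87 in the finest (33 against 120), assuming an even spread over age. Uneven ages would leave some cells smaller still. The analyses listed after the minimum do not produce reference limits, although the norms are the primary aim.

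The composition issue is one of definition. The documents show an uncontrolled mix and opposing exclusions; they do not show which way, or how far, the norms would be biased. The shifts calculated above are illustrations under assumed shares, deficits and correlations.

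**What to change.** Derive the norms by continuous, regression-based norming on the whole reference sample: a smooth age term, sex as covariate, and either a modelled SD or quantile regression, with pointwise confidence intervals for the limits. Drop the 120/153/199 standard for age-by-sex groups, or restrict partitions to those that meet it (sex alone, or up to three age bands alone for 120).

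Name the reference population. Show the norms both in children without an NDD diagnosis and in the full sample weighted to a stated NDD prevalence. Previous diagnosis is already among the demographic items collected. State that the IQ and psychiatric exclusions limit whom the norms describe. If predictive values are reported, give them at stated prevalences: with an assumed sensitivity and specificity of 0.80, PPV is 0.40/(0.40 + 0.10) = 0.80 at 50% cases but 0.08/(0.08 + 0.18) = 0.31 at 10%.

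The cost is plan wording and modest analysis work, with no new data. The price is an assumption of smooth change with age and wider limits at the youngest and oldest ages. On 400 children, precision is close to that of a 120-child group (SE 0.16) in the middle of the age range, but worse at the ends (about 0.19 to 0.22). If 30% had an NDD diagnosis (assumption), the 280 remaining children would give SEs of about 0.16 to 0.23, and up to about 0.27 at the ends with continuous age. The gain over two age bands by sex (SE 0.17) is therefore age-specific limits without treating each three-year band as homogeneous, rather than a smaller SE. Over single-year cells (SE 0.30) the gain is in precision as well.

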#### Sampling

We will account for variations across population and strive to identify the broad range of social and environmental influences on brain function and development. Such an approach may ultimately reveal a much more complex tapestry of etiological mechanisms than are typically derived from averaging over a relatively homogenous sample. Based on our own experience and previous sampling frame to access a representative sample of the larger heterogeneous population of children (66–69) and using three broad dimensions of phonological processing abilities, executive skills and processing speed (70) with latent factor analysis (71), we estimated that the final sample size is 400 children (half boys and half girls) for power analysis of 0.8, a confidence level of 0.05, and a type I error to detect medium to small effects over the study’s duration (72) Because we except a 20% attrition rate at each critical step: the enrollment process till the data collection completion, we have estimated that 786 participants (Figure 1) will be needed to provide a comprehensive understanding of changes through the test batteries assessing numerous factors impacting brain functioning.

#### Hypothesis testing framework

Hypotheses will be tested at the α = 0.05 level after adjustment for multiple tests. Significant statistics only will be converted to indices of effect size and their associated confidence interval. The primary analytical framework will be nested linear mixed models with random effects (LMEs), and Cox proportional hazards models to handle quantitative predictor variables and categorical variables.

For LMEs, the primary effects of interest will generally be the interaction between independent variables and time (e.g., the visit number). Analyses will be performed with multiple levels of nesting (e.g., site, devices) that are not of intrinsic interest, as well as nesting within participants over time, allowing all data to be used for wide analyses. Age and gender will be specified as co-variables and others such as demographic and other background variables will be specified upon scientific and empirical considerations.

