### Research questions and hypotheses

Combining cognition, emotion, behavioral, and brain measurements at once through an unmodified tablet is a novel approach that could facilitate NDD evaluation in real-life practice at large scale. Overall, we hypothesize that brain functioning e-screening with XAI4Kids® in real life practice, will be as or more feasible and capable of capturing the heterogeneity of NDDs in the population, and ultimately serve as a first instance transdiagnostic evaluation for NDDs.

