### Study design

EPIDIA4Kids is an observational uncontrolled multi-center study (several cities in France) during which no treatment or placebo will be administered. Complementing children’s assessment at baseline (T0), a subsample of 10% of the participants will be re-assessed after 2 months (end-T2). At least one of the parent or legal representatives and children will also answer questionnaires and will be interviewed using a semi-structured instrument (Figure 1).

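### Effect sizes and confidence intervals are limited to significant results, which inflates what is reported where power is low and leaves non-significant model-based comparisons without an interval

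*Protocol article*

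**What the plan says.** The protocol article, Hypothesis testing framework, sets the filter first: "Hypotheses will be tested at the α = 0.05 level after adjustment for multiple tests". It then states the reporting rule: "Significant statistics only will be converted to indices of effect size and their associated confidence interval". The adjustment method is not named. The same section makes linear mixed models and Cox models the primary framework, with interactions with time as the effects generally of interest.

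The study asks questions that need estimates. Research questions and hypotheses expects that the tool "will be as or more feasible and capable of capturing the heterogeneity of NDDs in the population". Table 1 asks whether the e-assessment is at least as acceptable and at least as feasible as paper screening, predicts strong correlations between the two, and compares follow-up with baseline scores.

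The only other provision for intervals is under Descriptive statistics: adjusted Wilson intervals for proportions, where appropriate. The Reference interval section deals with the precision of percentiles, not with tests.

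**The concern.** An estimate that is shown only when it passes a significance threshold is, on average, too far from zero. The lower the power, the larger the excess. When the threshold is strict or power is low, the ordinary 95% interval attached to such an estimate also covers the truth less than 95% of the time.

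The second consequence is what goes missing. If an e-versus-paper comparison is not significant, only its interval shows whether the tools are close or the data are merely uninformative. The same holds for change over time, where a stable score is expected to give a non-significant result. The rule withholds the interval in exactly these cases.

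At stake is how small effects, the retest results and the EEG results are read, and whether a null comparison can be interpreted.

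**Working it through.** **Inputs from the protocol article**
- Sampling: "we estimated that the final sample size is 400 children (half boys and half girls) for power analysis of 0.8", that is 200 v 200 by sex; target described as "a type I error to detect medium to small effects over the study’s duration", with no numeric effect.
- Study design: "a subsample of 10% of the participants will be re-assessed after 2 months (end-T2", about 40 of 400 (79 of 786). The Figure 1 legend gives about 500 returning, which does not fit 10%; the text figure is used here.
- Electro-encephalographic measures: 50 children.

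**Assumptions**
- Two-sided tests.
- True d of 0.10 to 0.50 and true r of 0.20 to 0.50.
- Adjusted alpha of 0.05/17 = 0.0029 (Bonferroni over the 17 rows of Table 3).

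**The plan's own figure.** The plan expects a "20% attrition rate at each critical step" and concludes that "we have estimated that 786 participants (Figure 1) will be needed". With three steps, as Figure 1 suggests, 400/0.8³ = 781.25, so 782 against 786 stated: reproduced closely. The base of 400 cannot be checked without a numeric effect. At 200 v 200 and two-sided 0.05, power is 80% at d = 0.28 and 52% at d = 0.20. The point made here does not depend on the 786.

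**Inflation.** Let m = true effect/SE and c = the critical value (1.960 at 0.05; 2.974 at 0.05/17). Power is P = Φ(m − c) + Φ(−m − c). The mean reported effect divided by the true effect is

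1 + [φ(c − m) − φ(c + m)] / (m·P).

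For 200 v 200, SE = √(2/200) = 0.10. At d = 0.20, m = 2:
- alpha 0.05: 1 + (0.3986 − 0.0002)/(2 × 0.516) = 1.39, a mean reported d of 0.28.
- alpha 0.05/17: P = 0.165, and 1 + 0.248/(2 × 0.165) = 1.75, a mean reported d of 0.35.

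**Coverage** of the ordinary 95% interval among significant results is P(|x − m| < 1.96 and |x| > c)/P, where x is normal with mean m and SD 1. At d = 0.20:
- alpha 0.05: (0.975 − 0.484)/0.516 = 95%.
- alpha 0.05/17: (0.975 − 0.835)/0.165 = 85%.

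| 200 v 200 | Ratio (coverage), 0.05 | Ratio (coverage), 0.05/17 |
|---|---|---|
| d = 0.10 | 2.45 (84%) | 3.34 (0%) |
| d = 0.20 | 1.39 (95%) | 1.75 (85%) |
| d = 0.28 | 1.13 (97%) | 1.33 (94%) |
| d = 0.50 | 1.00 (95%) | 1.01 (97%) |

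**Retest subsample, n = 40.** SE of a standardized change = 1/√40. At 0.20, m = 1.265 and P = 0.244. The ratio is 1 + (0.313 − 0.002)/(1.265 × 0.244) = 2.01, with coverage 90%. At 0.50 it is 1.07. With 79 children the ratio at 0.20 is 1.52. With 500 it would be about 1.00 (m = 4.47).

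**Correlations** (Fisher z, SE = 1/√(n − 3), simulated):

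| n | True r | Mean reported, 0.05 | Mean reported, 0.05/17 |
|---|---|---|---|
| 50 | 0.30 | 0.39 | 0.47 |
| 50 | 0.50 | 0.50 | 0.53 |
| 400 | 0.20 | 0.20 | 0.21 |
| 400 | 0.30 | 0.30 | 0.30 |

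**What is withheld.** At 200 v 200 a standardized difference has an interval of about ±1.96 × 0.10 = ±0.20. That would show which effects a null result rules out. Under the rule it is not produced.

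**The case against.** The strongest defence is that the main results are barely touched. The primary validity correlations use about 400 children and are expected to be strong, and at that size the filter does almost nothing to an r of 0.2 or more. A reader might infer that the tool's main validity figures would be overstated; the calculation does not support that. A correlation is also already an effect size, and the rule may be meant only for test statistics such as F or t. The wording leaves this open. The 200 v 200 split is by sex, so the d figures illustrate the mechanism and are not a tool-versus-paper contrast.

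A reader might also infer that reported intervals lose their coverage in general. They do not: at d = 0.20 and alpha 0.05 coverage stays at 95%, and it falls only with low power or a strict threshold.

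A third tempting reading is that no result could support the tool being as acceptable or as feasible. That goes too far. The quantitative acceptability and feasibility outcomes are proportions, and Wilson intervals for them are not tied to significance. Table 1 words the testable hypotheses as superiority and gives no margin, so reporting intervals would not by itself make an equality claim testable.

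What remains: a Wilson interval for one proportion is not an interval for the difference between tools, and it covers no mean difference, mixed-model, Cox, ANOVA or regression result. No passage in the protocol article reverses the rule for these.

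**Conclusion.** The point stands in limited form and should be fixed. The rule is explicit and current, so an analysis plan that followed it would carry it forward.

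The inflation is material for small effects, strict adjustment and the small subsamples: 39% to 75% at d = 0.20 with 200 v 200, about twofold for a change of 0.20 in 40 children, and 0.39 to 0.47 for a true r of 0.30 in 50. It is moderate (13% to 33%) at d = 0.28, where unadjusted power is 80%. It is 1% or less at d = 0.5 with 200 v 200, and at n = 400 it is about 6% at most for r = 0.20 and nil for r = 0.30.

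The loss of intervals for non-significant model-based comparisons does not depend on these assumptions. It follows directly from the sentence. The effect sizes, two-sidedness, the divisor of 17 and the 40 retested children are assumptions.

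The rule changes no data collection, sample size, model or test, and descriptive summaries are reported regardless of significance. It is therefore a reporting defect that can be corrected before results are seen.

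**What to change.** Replace the sentence in Hypothesis testing framework with:

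*Effect sizes with 95% confidence intervals will be reported for every pre-specified hypothesis, whatever its p-value; adjusted p-values will be given beside them.*

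With no selection, the expected ratio of reported to true effect is 1.00 and coverage is 95% at every effect size. The cost is one sentence and longer tables. If the sponsor wants to claim formally that the tool is as acceptable or as feasible as paper screening, a margin must be stated as well; the replacement sentence does not supply it.
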